#### Process evaluation

Alongside the RCT, we will conduct a process evaluation by interviewing patients, GPs, and specialists with the purpose of identifying barriers and facilitators of GP-based prostate cancer follow-up care. The methodology of this process evaluation will be described separately. If the results of the trial support the cost-effectiveness of GP follow-up care, the results of the process evaluation are expected to enable the transition of follow-up care to the GP.

### Power calculation

A total of 390 patients will be entered in this trial, 195 patients in each arm. Based on the objectives, the sample size is calculated separately for patients treated with prostatectomy (*n* = 270) and patients treated with radiotherapy (*n* = 120).

#### Adherence to the prostate cancer surveillance guideline and time from a BCR to prostate cancer retreatment decision making

With a sample of 270 patients who have been treated with prostatectomy, the prospective design will allow for testing of the main effect of GP-based versus specialist-based follow-up care on adherence to the prostate surveillance guideline, as represented by the timing and frequency of PSA assessments. It is expected that 90% of the patients in the usual care group will be assessed according to the guideline, defined as 4 PSA measurements in the study period of 2 years. This is in line with the observed adherence to PSA testing recommendations in a previous randomized controlled trial of shared care for follow-up of men with prostate cancer [24]. We consider an adherence percentage as low as 80% (10 percentage points non-inferiority margin) in the GP-based group as acceptable and lower adherence percentages as unacceptable. With 270 prostatectomy patients we have 86% power at a one-sided significance level of 5%.

We will also evaluate the difference between arms in time from a BCR to prostate cancer retreatment decision-making. Based on data of a retrospective cohort study of 1340 patients who were treated with prostatectomy at the Antoni van Leeuwenhoek Hospital and expert opinion, an acceptable mean time to decision-making is thought to be 30 days. We will evaluate whether the time to decision-making is substantially longer in the GP-arm than the specialist-based arm. We consider the maximally acceptable average time to decision-making in the GP-based arm as 90 days (60 days non-inferiority margin). In the absence of empirical data on the standard deviation (SD) for the time to decision-making, we assume an SD of 20 days in the specialist-arm and 60 days in the GP-arm. With 270 prostatectomy patients we expect a total of 7 patients with a BCR in each arm, which enables us to investigate the time from a BCR to prostate cancer retreatment decision making.

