### Randomization

In total, 390 consenting men will be randomized to either the GP-based (*n* = 195) or specialist-based (n = 195) follow-up care group. Randomization will be on a 1:1 ratio. The minimization technique will be applied using a randomization program (ALEA, FormVision, Abcoude, the Netherlands) to balance usual care with the intervention within a hospital on type of primary treatment (prostatectomy or radiotherapy) and clinical stage (according to the European Association of Urology (EAU) risk scores: low risk; intermediate risk; high risk [10]). Blinding of participants and clinicians is not possible due to the nature of the intervention.

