### Data analysis

#### Primary study outcomes

All analyses will be performed based on the intention-to-treat principle. Analyses will first be performed to evaluate the comparability of the groups at baseline on sociodemographic and clinical variables. The percentages of patients with four PSA tests in a period of 2 years will be compared in the two arms by using chi-square tests and multivariable by logistic regression.

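### The primary adherence test is powered on the 270 prostatectomy patients, but the objective and the analysis as written cover all 390 randomised, so the primary population is not fixed

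*Protocol article*

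**What the plan says.** All places are in the Protocol article.

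- **Power calculation:** "A total of 390 patients will be entered in this trial, 195 patients in each arm". In the same section, "the sample size is calculated separately for patients treated with prostatectomy" (270) and for those treated with radiotherapy (120), with the objectives given as the reason.
- **Power subsection on adherence and time from biochemical recurrence:** "With a sample of 270 patients who have been treated with prostatectomy, the prospective design will allow for testing of the main effect" of the follow-up model on adherence. It expects 90% adherence under usual care, sets a 10-point margin, and concludes: "With 270 prostatectomy patients we have 86% power at a one-sided significance level of 5" per cent.
- **Data analysis, Primary study outcomes:** every analysis is by intention to treat. "The percentages of patients with four PSA tests in a period of 2 years will be compared in the two arms", using chi-square tests and a multivariable logistic regression. Treatment type is not mentioned.
- **Data analysis, Secondary study outcomes:** time from biochemical recurrence to the retreatment decision is expressly confined to prostatectomy patients.
- **Randomization:** "Randomization will be on a 1:1 ratio", with minimisation "to balance usual care with the intervention within a hospital on type of primary treatment (prostatectomy or radiotherapy) and clinical stage".
- **Objectives and hypotheses, Population and setting, and Table 1:** these cover survivors of localised disease after either treatment, with a single PSA schedule.

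**The concern.** Adherence and time from biochemical recurrence are sized in the same subsection on the same 270 patients. Only the second carries the prostatectomy restriction into the analysis section. Read plainly, the adherence comparison therefore includes all 390 men, while its power is quoted for 270.

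The choice of set decides which question the trial answers. A test in the 270 leaves 120/390 = 31% of randomised men outside the confirmatory result, although the Discussion draws its conclusion for localised prostate cancer patients in general. A test in all 390 answers the stated objective, and the quoted power is then too low. The trial is unblinded, so the set should be on record before outcomes are compared between arms.

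**Working it through.** **Inputs from the article:** usual-care adherence 90%; margin 10 percentage points; one-sided 5%; 1:1 allocation with minimisation on treatment type, so 270 gives about 135 per arm, 390 gives 195 and 120 gives about 60.

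**Inputs assumed:** true adherence of 90% in the GP arm. The article does not state it, but it fits the hypothesis of equal effectiveness. No missing primary endpoint data, since the 20% attrition in the article refers to questionnaires.

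**Formula** (unpooled normal approximation, n per arm):

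power = Φ( [0.10 − (pC − pG)] / SE − 1.645 ), with SE = √( [pC(1 − pC) + pG(1 − pG)] / n )

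**1. The article's own figure.** n = 135, 90% in both arms: SE = √(0.18/135) = 0.0365. Then 0.10/0.0365 = 2.739, less 1.645 = 1.094, and Φ(1.094) = 86.3%. The stated 86% reproduces.

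**2. All randomised patients.** n = 195: SE = √(0.18/195) = 0.0304. Then 0.10/0.0304 = 3.291, less 1.645 = 1.647 from unrounded values, and Φ(1.647) = 95.0%.

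**3. Range under less favourable assumptions.** With 20% lacking the endpoint, n falls to 108 or 156 per arm. With true GP adherence of 88%, the numerator becomes 0.10 − 0.02 = 0.08 and the variance sum becomes 0.09 + 0.1056 = 0.1956.

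| Set analysed | n per arm | Assumption | Power, one-sided 5% |
|---|---|---|---|
| 270 prostatectomy | 135 | 90%/90%, complete data | 86.3% |
| All 390 | 195 | 90%/90%, complete data | 95.0% |
| 120 radiotherapy | 60 | 90%/90%, complete data | 57.2% |
| 270 prostatectomy | 108 | 20% lack the endpoint | 78.9% |
| All 390 | 156 | 20% lack the endpoint | 90.3% |
| 270 prostatectomy | 135 | true GP adherence 88% | 67.6% |
| All 390 | 195 | true GP adherence 88% | 81.1% |

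**4. Sensitivity to the variance formula.** With the restricted-null (Farrington-Manning) variance, power is 83.8% for 270 and 93.8% for 390. The gap between the two sets remains.

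**5. Room for covariates.** At 90% adherence, 0.10 × 390 = 39 patients are expected to be non-adherent. A model with arm (1 term), treatment type (1), three risk groups (2) and 12 hospitals as fixed effects (11) has 15 terms, or 39/15 = 2.6 events per term. Without hospital there are 4 terms, or 39/4 ≈ 10 events per term.

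**The case against.** Sizing by treatment group is declared and deliberate: prostatectomy patients drive adherence and recurrence time, radiotherapy patients drive side-effect management, and all 390 drive the patient-reported outcomes. Sizing on a subgroup does not exclude the others from analysis. If all 390 are analysed, 86% is merely a conservative statement. If 270 are analysed, a comparison of the two arms is still an accurate description. An analysis plan that is not shown may settle the matter.

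Much of this stands, and it rules out three stronger readings:

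- **That one of the two sections must be wrong.** Each can be true on its own. What is missing is a statement that joins them.
- **That power is being thrown away.** That follows only if the test is limited to the 270, and the article nowhere says that radiotherapy patients are excluded from it. On the natural reading no patient is discarded, and the power is understated.
- **That the primary comparison is unadjusted.** The chi-square test is, but a multivariable logistic regression is planned as well. Leaving its covariates to an analysis plan is normal.

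The declared one-sided 5% level is a separate matter and need not change to resolve this one.

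The objection does not remove the mismatch itself. The article speaks of the primary population in both its power and its analysis sections, and the two do not name the same set.

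**Conclusion.** The concern holds as a mismatch between the powered and the analysed population. The 86% is correct for 270 prostatectomy patients. It is not the power of the intention-to-treat comparison as written, which is about 95% at the same one-sided 5%. That figure assumes 90% adherence in both arms and complete endpoint data. Under the two less favourable assumptions examined one at a time it is about 90% and about 81%, against 79% and 68% for the 270.

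The error is in the conservative direction if all 390 are analysed. The practical weakness is that the primary set, and with it the population to which a non-inferiority conclusion applies, is not fixed. Radiotherapy patients alone (57% power) could not support a confirmatory conclusion of their own, so they are covered by the primary result only if they are in the primary set.

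**What to change.** - State in both the power subsection on adherence and the primary analysis section that the primary non-inferiority analysis uses all 390 randomised patients.
- Restate power as about 95% at one-sided 5%, with its assumptions and the range above.
- Make the primary estimate a risk difference, with its one-sided 95% confidence limit compared with the 10-point margin, stratified by or adjusted for treatment type and EAU risk group.
- Handle hospital parsimoniously, for example by pooling centres or as a random effect, because only about 39 non-adherent patients are expected.
- Report the prostatectomy and radiotherapy estimates as secondary.
- If the sponsor means the 270 to be the primary set, say so in the primary analysis section, keep the 86%, and limit the primary conclusion to prostatectomy patients.

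**Cost:** changes to the text and to the analysis code. PSA counts are already to be abstracted from medical records as the primary outcome, without limit by treatment, so no new patients or data are needed. The change should be dated before outcomes are compared between arms. The downside is that a pooled estimate applies one margin to both treatment groups. The separate estimates would show whether that is reasonable, although the radiotherapy estimate will be imprecise.

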#### The management of treatment-related side effects as experienced by patients

With a sample of 120 patients who have been treated with radiotherapy, we are able to test the management of treatment-related side effects as experienced by patients. Hence, we will focus on questions from three scales of the “Assessment of Patients’ Experience of Cancer Care (APECC) survey” (information exchange; physicians’ affective behavior; and physicians’ knowledge) [44]. We will use the mean score of those three scales to measure patient satisfaction with the follow-up care. Arora and colleagues observed SDs between 15.8 and 24.9 for these three scales [44]. We assume that these SDs are generalizable to our hospital patient group. For a SD of 15.8, power is 80% to detect a clinically relevant difference of 8.1 points (effect size = 8.1/15.8 = .51) with 60 patients in each group (two-sided alpha 5%) [53].

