#### Patient-reported outcomes

For the patient-reported outcomes (e.g. HRQOL, prostate-specific anxiety, etc.) we will compare changes in mean questionnaire scores over time between the usual care and the intervention group. Based on 390 patients and a survey attrition of 20%, power is at least 80% to detect a difference in questionnaire-based outcomes between patients who had their follow-up at their GP or specialist with an effect size of 0.1, at a two sided-significance level of 5%. With this sample size we will be able to detect clinically meaningful differences [53].

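### The 80% power for the APECC mean score treats all 120 radiotherapy patients as complete responders; with the plan's own 20% survey attrition it is about 70% at the plan's SD of 15.8

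*Protocol article*

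**What the plan says.** The power calculation in the protocol article splits the sample into 270 prostatectomy and 120 radiotherapy patients. Its subsection on management of treatment-related side effects rests on the second group: "With a sample of 120 patients who have been treated with radiotherapy". The outcome is the mean of three APECC scales (information exchange, physicians' affective behaviour, physicians' knowledge). The source study "observed SDs between 15.8 and 24.9 for these three scales", and the article assumes that these SDs carry over. It then states "For a SD of 15.8, power is 80% to detect a clinically relevant difference of 8.1 points", with 60 patients in each group and "two-sided alpha 5" per cent.

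The next subsection, on patient-reported outcomes, starts from a different completeness assumption: "Based on 390 patients and a survey attrition of 20" per cent.

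Table 2 lists APECC as a survey. The section on secondary study outcomes has it assessed at T0, T1, T2 and T3, and the data analysis section tests questionnaire scores with mixed effects models. Neither section restricts APECC to radiotherapy patients.

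**The concern.** Two adjacent paragraphs plan questionnaire outcomes in the same trial on different completeness assumptions. The side-effect paragraph uses every enrolled radiotherapy patient and has nothing in reserve, so any non-response takes power below the stated 80%.

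This matters because the hypothesis is that GP-based care is as effective as specialist care, and the Discussion expects the arms not to differ significantly. With a two-sided difference test at 70% power, there is a 30% chance of a non-significant result when the arms truly differ by the 8.1 points that the plan calls clinically relevant. That result could be read as reassurance.

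Two further points are unsettled. The SD in the calculation is the lowest of the quoted single-scale values, while the endpoint is a mean of three scales whose SD is not given. And the document does not say consistently whether the test covers radiotherapy patients or everyone randomised.

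**Working it through.** **Inputs from the protocol article.** Difference 8.1 points; SD 15.8; 60 per arm (120 radiotherapy patients, 1:1); two-sided alpha 5%; survey attrition 20%; single-scale SDs 15.8 to 24.9; 390 patients in total, 195 per arm.

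**Method.** Two-sample t test, noncentral t, with noncentrality = difference / (SD × √(2/n)) for n per arm.

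**1. The plan's own figure.** Effect size 8.1/15.8 = 0.513. With n = 60, noncentrality = 8.1 / (15.8 × √(2/60)) = 2.81 and power is 79.5% (80.2% by normal approximation). The stated 80% reproduces. By t test 61 per arm are needed to reach 80%, so there is no margin.

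**2. With the plan's attrition.** 60 × 0.80 = 48 per arm. Noncentrality = 8.1 / (15.8 × √(2/48)) = 2.51 and power is 70.0% (70.9% by normal approximation). The standardised difference detectable with 80% power is 0.578, which is 0.578 × 15.8 = 9.1 points. To keep 80% power after this attrition, about 61/0.80 ≈ 76 per arm would have to be enrolled, against 60.

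**3. The SD of the mean score.** The SD of a mean of three scores cannot exceed the mean of their SDs. With one scale at 15.8 and the others at most 24.9, the ceiling is (15.8 + 24.9 + 24.9)/3 = 21.9, reached only under perfect correlation. Below that,

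SD of mean = (1/3) × √(Σ s² + 2r Σ sᵢsⱼ).

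The middle SD and the inter-scale correlation r are not in the document. Assuming a middle SD of 20.35 (the midpoint of 15.8 and 24.9), Σ s² = 1283.8 and Σ sᵢsⱼ = 1221.7, which gives:

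| Assumed r | SD of mean | Power, 48 per arm |
|---|---|---|
| 0.2 | 14.0 | 80% |
| 0.4 | 15.9 | 70% |
| 0.5 | 16.7 | 65% |
| 0.6 | 17.5 | 61% |
| 0.8 | 19.0 | 54% |
| Ceiling (15.8, 24.9, 24.9; r = 1) | 21.9 | 44% |

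So 15.8 can be too low or too high for the mean score, depending on a correlation that the document does not report.

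**4. All randomised patients.** 195 × 0.80 = 156 per arm. Power for 8.1 points is 99% at SD 15.8 and 90% at SD 21.9.

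**The case against.** **The arithmetic is right, and its SD condition is stated.** This stands. The 80% follows from its inputs, the article names the SD it used, and it shows the full range. The fault is a missing attrition allowance, inconsistent with the next paragraph; it is not a calculation error.

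**Averaging scales lowers the SD, so 15.8 need not be optimistic.** This stands too. With the assumed middle SD, the SD of the mean is 15.0 at a correlation of 0.3, below the plan's value. A reader might put the largest single-scale SD, 24.9, into the calculation and infer that power collapses to 35%. The document does not support that: 24.9 belongs to a single scale, the endpoint is the three-scale mean, and its SD cannot exceed 21.9. Nor can the document show that 15.8 is too low.

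**The planned mixed model would be more efficient than a t test.** This is partly right. Baseline adjustment at an assumed baseline to follow-up correlation of 0.5 would give about 82% with 48 per arm at SD 15.8, and a mixed model keeps partly observed patients. But the stated 80% is a plain two-sample figure, takes no credit for repeated measures, and gives no correlation from which to claim it.

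**The analysis section does not confine APECC to radiotherapy patients.** This limits the point. If all randomised patients are analysed, the test is well powered. The shortfall holds for the test as described in the power calculation, so the two places need to be aligned.

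**Conclusion.** The point holds. For a test in radiotherapy patients, the stated 80% becomes 70% once the plan's own 20% attrition is applied at its own SD of 15.8. This rests on three assumptions: that the attrition given for patient-reported outcomes applies to APECC, which is a questionnaire in the same patients; that lost patients contribute nothing; and that the test is a two-sample t test, as in the article's own calculation.

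The SD of the mean score is an open question rather than a demonstrated error. Over assumed correlations of 0.2 to 0.8, power with 48 per arm runs from 80% to 54%, with 44% as the floor at the SD ceiling.

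It would go too far to conclude that the trial as a whole cannot answer this question. The outcome is secondary, the primary endpoint is untouched, and the questionnaire data described in the outcome and analysis sections are enough for a well-powered comparison in all randomised patients.

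**What to change.** State that the APECC mean score is compared between arms in all 390 randomised patients, adjusted for treatment type, with radiotherapy patients as a subgroup. Give the power after 20% attrition (156 per arm): 99% at SD 15.8 and 90% at SD 21.9, noting the assumption that these SDs also apply to prostatectomy patients.

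If the test is to stay within radiotherapy patients, say so in the analysis section as well, restate the power as about 70% at SD 15.8 after 20% attrition (detectable difference 9.1 points), and justify the SD for the mean of the three scales, including the inter-scale correlation assumed. Any gain claimed from baseline adjustment should be given with its correlation.

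The cost is wording and a restated figure; no further data collection is described as necessary, since the outcome section does not limit the questionnaire to one treatment group. The downside is small: either a main estimate averaged over both treatment types, or a less favourable stated power.

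### The 80% power for the APECC comparison in radiotherapy patients counts every man entered as evaluable, while the next paragraph plans 20% survey attrition; on the same two-sample basis that leaves about 70%

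*Protocol article*

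**What the plan says.** The Power calculation section sets the total ("A total of 390 patients will be entered in this trial, 195 patients in each arm") and divides it into 270 prostatectomy and 120 radiotherapy patients, with the sample size worked out separately for each group.

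The subsection on management of treatment-related side effects opens "With a sample of 120 patients who have been treated with radiotherapy" and takes the APECC survey as the outcome. Three of its scales are averaged: "We will use the mean score of those three scales to measure patient satisfaction with the follow-up care". The cited source "observed SDs between 15.8 and 24.9 for these three scales". At the lowest of these SDs, "power is 80% to detect a clinically relevant difference of 8.1 points (effect size = 8.1/15.8 = .51) with 60 patients in each group", two-sided at 5%. The subsection does not mention attrition.

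The subsection that follows, on patient-reported outcomes, begins its own calculation with "Based on 390 patients and a survey attrition of 20%, power is at least 80" per cent. Here attrition is part of the calculation.

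Table 2 lists the APECC as a patient survey. Under Secondary study outcomes, self-reported side-effect management is measured at T0, T1, T2 and T3 alongside the other questionnaires. Under Data analysis, APECC scores go into the same mixed effects approach as the other instruments.

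**The concern.** Two adjacent paragraphs of one power section treat the same kind of data differently. One reduces the questionnaire sample by 20%. The other treats everyone entered as a respondent. The 390 men in the second paragraph include the 120 in the first, and the reminder and telephone procedure under Data collection gives the APECC no special handling. If 20% loss is a fair expectation for the questionnaires in general, it is a fair expectation for this one.

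The APECC comparison is the purpose the article gives for the radiotherapy sample of 120. It is also powered as a two-sided test of difference with no margin, while the Discussion expects no significant difference between arms. If the test comes out non-significant, the stated power is what a reader will use to judge how much that result says. An overstated figure makes the result look more informative than it is.

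**Working it through.** **Inputs**

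- Radiotherapy patients entered: 120 (Power calculation).
- Allocation: "Randomization will be on a 1:1 ratio" (Randomization), hence 60 per arm.
- Difference Δ = 8.1 and SD σ = 15.8, so d = 8.1/15.8 = 0.513; two-sided α = 5% (side-effects subsection).
- Survey attrition: 20% (patient-reported outcomes subsection).

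**Step 1: reproduce the stated figure.** In the normal approximation, power = Φ(Δ / (σ√(2/n)) − 1.96).

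For n = 60: σ√(2/60) = 15.8 × 0.1826 = 2.885; 8.1/2.885 = 2.808; 2.808 − 1.96 = 0.848; Φ = 80.2%. The noncentral t gives 79.5%. The stated 80% is therefore right for 60 men analysed per arm, and 60 is all who are entered.

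**Step 2: apply the planned attrition.** 60 × (1 − 0.20) = 48 per arm.

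For n = 48: 15.8 × 0.2041 = 3.225; 8.1/3.225 = 2.511; 2.511 − 1.96 = 0.551; Φ = 70.9%. The noncentral t gives 70.0%.

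**Step 3: vary the attrition.** SD 15.8, difference 8.1:

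| Attrition | Analysed per arm | Power (normal) | Power (t) |
|---|---|---|---|
| 0% | 60 | 80.2% | 79.5% |
| 10% | 54 | 75.9% | 75.2% |
| 15% | 51 | 73.5% | 72.7% |
| 20% | 48 | 70.9% | 70.0% |
| 25% | 45 | 68.1% | 67.2% |

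**Step 4: difference detectable with 80% power.** (1.96 + 0.842) × σ√(2/n). With 60 per arm: 8.1 points (t: 8.15). With 48 per arm: 2.802 × 3.225 = 9.0 points (t: 9.13, and 9.13/15.8 = 0.58 SD).

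**Step 5: entry needed to keep 80% for 8.1 points, as a measure of the gap only.** 60/0.8 = 75 per arm, 150 in total. The t-test needs 61 analysed, so 61/0.8 rounds up to 77 per arm, 154 in total. The plan enters 120.

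**Step 6: what adjustment for baseline could recover.** The article gives no correlation, so r here is assumed. With a baseline-adjusted comparison, d becomes 0.513/√(1 − r²). With 48 per arm (t), power is 74% at r = 0.3, 77% at r = 0.4 and 82% at r = 0.5.

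**Step 7: the SD, as a side check.** The variance of the mean of three scales with common correlation r is [Σs² + 2r Σsᵢsⱼ]/9. The outer SDs are 15.8 and 24.9; the middle one is not given. Setting the result to 15.8² = 249.64 and solving for r:

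- middle SD 15.8: r = (2246.76 − 1119.29)/(2 × 1036.48) = 0.54;
- middle SD 24.9: r = (2246.76 − 1489.66)/(2 × 1406.85) = 0.27.

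So 15.8 is attainable for the three-scale mean if the scales correlate no more strongly than some value between 0.27 and 0.54. At the other end of the quoted range, SD 24.9, t-test power is 42% with 60 per arm and 35% with 48.

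**The case against.** **The 80% is not a miscalculation.** It is conditional on an SD of 15.8 and 60 men per group, and on those terms it reproduces. This stands: the fault is an omitted allowance, not wrong arithmetic.

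**The 20% was written for something else.** It appears in the paragraph on the 390 men, with quality of life and anxiety as the examples. Carrying it over to the APECC is an inference. It is a well-supported one, since the APECC is a questionnaire given to a subset of the same men on the same schedule.

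**The planned analysis is not a two-sample test of complete cases.** This is the strongest objection. A mixed model over T0 to T3 keeps men with partial follow-up and can draw on correlation between visits, so a reader who infers that the trial's real power is 70% goes too far. At an assumed baseline correlation of 0.5 the loss is made good (82%); at 0.3 it is not (74%). But the article states no correlation, and its 80% matches the simple two-sample formula. The printed figure therefore cannot rest on the mixed model.

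**The SD.** A reader might infer that the SD is wrong and that power is far below 70%. The documents do not support that. The middle SD and the inter-scale correlations are not given, 15.8 is attainable for a mean of three scales, and the article discloses the whole range. What stands is a caution: the smallest single-scale SD is used for a composite without a reason.

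**Reach.** The Data analysis section does not restrict the APECC analysis to radiotherapy patients. With all 390 men and 20% loss, 156 per arm remain and power for 8.1 points at SD 15.8 exceeds 99%. The weakness belongs to the radiotherapy-only comparison for which the 80% is stated.

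**Conclusion.** The point holds within these limits. On the article's own two-sample basis and its own 20% attrition, power for an 8.1-point APECC difference among radiotherapy patients is about 70%, not 80%. The risk of missing such a difference rises from about 20% to about 30%. Equivalently, 80% power applies to about 9.1 points (0.58 SD).

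This rests on SD 15.8, a two-sided 5% test, equal loss in both arms (48 each), and applying the 20% questionnaire attrition to the APECC. Even 10% loss would bring power to about 75%.

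It does not show that the planned mixed model has only 70% power, that 15.8 is the wrong SD, or that the trial is too small. Nor does it touch the primary outcome, which comes from medical records rather than questionnaires.

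**What to change.** In the side-effects subsection of Power calculation, do one of the following:

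1. State that 48 evaluable men per arm are expected after 20% attrition, with about 70% power for 8.1 points at SD 15.8, or 80% power for about 9.1 points (0.58 SD).
2. Base the power on the mixed model named under Data analysis, stating the assumed correlation and its source and keeping the 20% attrition. With 48 per arm, an assumed baseline correlation of 0.3 to 0.5 would give about 74% to 82%.

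In either case, say why 15.8 is taken as the SD of the three-scale mean, and show the power for larger SDs within the quoted range.

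The change is to wording only. No patients are added, and no endpoint or analysis changes. The one cost is a less favourable stated power or detectable difference, unless a supported correlation justifies the higher figure.
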